### Procedures

Participant enrollment will be conducted through a face-to-face clinical interview with a trained psychologist or psychiatrist to confirm the diagnosis of ADHD and assess potential comorbidities based on *DSM-5* (*Diagnostic and Statistical Manual of Mental Disorders, Fifth Edition*) criteria.

Following informed consent and completion of baseline assessments, participants will be stratified by diagnostic status (ADHD vs neurotypical control). Within each stratum, the random allocation sequence will be generated by an independent research coordinator (not involved in recruitment or outcome assessment) using computer-generated permuted blocks of variable size with a 1:1 allocation ratio. This stratified block design ensures balanced group sizes over time and equal distribution of diagnostic groups across conditions.

The allocation sequence will be implemented using sequentially numbered, opaque, sealed envelopes prepared in advance by the independent research coordinator. Treating clinicians or research assistants will enroll participants and open the next envelope only after baseline measures are completed, ensuring that upcoming assignments remain concealed from both participants and enrollment staff. Due to the nature of the intervention condition, blinding of participants and experimenters is not feasible; however, data analysts will remain blinded to group allocation and condition labels until the primary analyses are completed to minimize bias during statistical analysis.

As illustrated in Figure 1, cognitive and emotional assessments will be administered at 10 time points: preexposure (T0), immediately postexposure (T1), and weekly over an 8-week follow-up period (T2-T9). These assessments will be completed online within the study platform. ADHD-specific assessments will be conducted at 3 time points: T0, T1, and the final follow-up (T9). EEG data will be recorded continuously during the exposure session to capture real-time brain activity in response to the environmental condition.

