#### ADHD-Related Measures

To assess ADHD symptomatology and its functional impact, the following standardized instruments will be used:

ASRS: a widely used self-report questionnaire assessing the severity of ADHD symptoms across inattention and hyperactivity/impulsivity dimensions. All participants will complete the ASRS to enable dimensional modeling across the full sample.

Adult ADHD Quality of Life Questionnaire (AAQoL): a 29-item self-report scale measuring the impact of ADHD on quality of life across multiple domains [75]. This measure will be administered to participants in the group with ADHD.

ADHD Clinical Outcome Self-Report (ACOS-Self): a 15-item routine clinical outcome measure assessing ADHD symptoms, associated mental health challenges, and functional impairments [76]. It will also be used only with participants formally diagnosed with ADHD.

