### Statistical Analysis

#### Outcomes

The primary outcomes of this study will be: (1) changes in indices of neural restoration and engagement (parietal-occipital alpha power, frontal midline theta, and frontal alpha asymmetry) from preexposure to postexposure; (2) performance on two cognitive tasks: Meta Mind (confidence score, accuracy, and reaction time) to evaluate metacognition, and Star Racer (completion time, error rate, and task-switching cost) to measure cognitive flexibility and executive control; and (3) ADHD symptom severity, assessed by ASRS, included in both diagnostic group comparisons and dimensional modeling across the full sample.

Secondary outcomes will include exploratory trajectories of emotional well-being assessed through EMA, as well as self-reported nature connectedness (NCI) and weekly real-life contact with natural environments. These repeated measures are intended to characterize short-term decay or change patterns after a single exposure. Clinical change in the group with ADHD will be measured with the ACOS-Self, and quality of life with the AAQoL. Measures of VR tolerability and cybersickness (VRSQ) will be analyzed descriptively and, where appropriate, as covariates to aid interpretation of cognitive and EEG outcomes.

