#### Statistical Methods

All analyses will follow an intention-to-treat approach and will be conducted using R (R Foundation for Statistical Computing). Statistical tests will be 2-tailed with a significance level of α=.05. Descriptive statistics will summarize sample characteristics. Baseline group differences will be assessed using Pearson chi-square tests for categorical variables and independent-samples *t* tests (or nonparametric equivalents) for continuous variables. Any variables showing systematic baseline imbalance will be considered as covariates in sensitivity analyses.

To evaluate the primary outcomes—changes from preexposure (T0) to immediate postexposure (T1) in EEG alpha power, cognitive performance (Meta Mind and Star Racer), and ASRS, we will implement linear mixed-effects models (LMMs) using the *lme4* package. Fixed effects will include exposure condition (real vs VR nature), diagnostic group (ADHD vs neurotypical), time (T0 vs T1, with T9 added where relevant to examine short-term maintenance), and their interactions. Participant will be entered as a random intercept; random slopes for time will be added where supported by convergence and model fit. The primary contrasts of interest are: (1) group × condition × time for alpha power in predefined frontal and parietal regions of interest, and (2) condition × time and group × time interactions for cognitive and ASRS outcomes.

For EEG data, log-transformed alpha power (8-13 Hz) will be averaged within each region of interest and exposure phase. Within-subject change scores (T1-T0, and T9-T0 where applicable) will be analyzed in the LMM framework described above. Exploratory time-resolved effects across the 20-minute exposure will be examined using cluster-based permutation tests on epoch-wise alpha power, with family-wise error controlled at 0.05. Effect sizes will be reported as Cohen *d* for pairwise contrasts and partial eta squared (η^2^_p_) for omnibus tests.

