Secondary outcomes include trajectories of emotional well-being assessed via weekly EMA, clinical functioning in the group with ADHD (ACOS-Self), quality of life (AAQoL), and nature connectedness (NCI). EMA scores over T0-T9 will be modeled with LMMs including fixed effects for time (treated as a continuous or categorical variable depending on fit), condition, group, and their interactions, with random intercepts for participants. ACOS-Self, AAQoL, and NCI change from T0 to T9 will be analyzed using separate LMMs with fixed effects for group, condition, and their interaction. Self-reported real-world nature and VR exposure during follow-up will be explored as time-varying covariates in additional models to probe their contribution to decay or maintenance of effects.

To incorporate a dimensional perspective, *z*-scored ASRS total and subscale scores will be included as continuous predictors in a restricted set of prespecified models [85] (eg, ASRS × condition × time interactions for alpha power and cognitive outcomes). These analyses will test whether attentional trait variation predicts sensitivity to environmental exposure across the full sample, without overparameterizing models.

Multiple-comparison control will be applied at the level of outcome families: EEG (regions of interest and key contrasts), cognitive tasks (Meta Mind and Star Racer indices), EMA trajectories, and clinical measures. Within each family, *P* values will be adjusted using false discovery rate procedures; unadjusted and adjusted values will both be reported.

Model assumptions (normality of residuals, homoscedasticity, and, where relevant, sphericity) will be checked using diagnostic plots and formal tests. If assumptions are violated, transformations or robust alternatives will be considered. Missing data will primarily be handled within the mixed-model framework under a missing-at-random assumption. In addition, sensitivity analyses will be conducted using multiple imputation and complete-case subsets (participants with data at least up to T1 and T9) to examine the impact of attrition on key inferences.

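### The stated model for ACOS-Self and AAQoL contains diagnostic-group terms that cannot be estimated, because both scales are collected only in the ADHD group; the same sentence, which also covers NCI, models change without a time term.

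*Protocol article*

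**What the plan says.** The secondary-outcome paragraph of Statistical Methods sets one model for three scales: "ACOS-Self, AAQoL, and NCI change from T0 to T9 will be analyzed using separate LMMs with fixed effects for group, condition, and their interaction".

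The section on ADHD-related measures limits two of those scales to one diagnostic group. Of the AAQoL it says "This measure will be administered to participants in the group with ADHD"; of the ACOS-Self, "It will also be used only with participants formally diagnosed with ADHD". The Outcomes section agrees: "Clinical change in the group with ADHD will be measured with the ACOS-Self, and quality of life with the AAQoL".

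The meaning of group is fixed where the primary models are described, as "diagnostic group (ADHD vs neurotypical), time (T0 vs T1, with T9 added where relevant to examine short-term maintenance), and their interactions". The same paragraph names the software and the random effect: "we will implement linear mixed-effects models (LMMs) using the *lme4* package" and "Participant will be entered as a random intercept; random slopes for time will be added where supported by convergence and model fit". The sentence on ACOS-Self, AAQoL and NCI restates neither.

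The Procedures section schedules ADHD-specific assessments at T0, T1 and T9. The section on emotional and psychological measures schedules NCI at baseline and final follow-up, in all participants.

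**The concern.** A factor with two defined levels is placed in a model whose data contain only one of them. The protocol does not say that controls complete ACOS-Self or AAQoL, and does not reduce the model to condition alone for these scales. A reader would expect a comparison of ADHD with neurotypical adults on clinical functioning and quality of life that the data cannot supply.

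A second difficulty sits in the same sentence. The outcome is described as change and the model as a mixed model, yet time is not among the fixed effects, although the preceding sentence on EMA lists it. It is unclear whether the model takes one difference score per person or the repeated scores, and neither reading gives a correct specification.

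At stake is the prespecified analysis of the two ADHD-only outcome scales, and for NCI the meaning of the reported coefficients. Several replacements are defensible (change score, baseline-adjusted T9 score, repeated measures with or without T1), so the choice should be in writing before outcome data exist.

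**Working it through.** The protocol gives no figure for this analysis, so there is nothing to reproduce. The check concerns what can be estimated.

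**Inputs.** 80 participants, 20 per diagnosis-by-condition subgroup (Power section), hence 40 with ADHD, 20 real and 20 VR. ACOS-Self and AAQoL in ADHD only. NCI in all 80. Fixed effects: intercept, group (g), condition (c), g × c.

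**1. Fixed effects, ADHD-only scales.** With g = 1 for everyone, each row of [1, g, c, g × c] is one of two patterns:

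- real nature: (1, 1, 0, 0), 20 rows
- VR nature: (1, 1, 1, 1), 20 rows

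The group column equals the intercept column, and the interaction column equals the condition column. Two distinct rows give rank 2 of 4. Intercept and condition alone give rank 2 of 2, so the condition effect is estimable once the group terms are removed. In R, a one-level group factor stops the fit with a contrasts error. With group coded as a numeric constant and repeated ADHD-only data, lme4 drops the redundant columns and returns the condition estimates.

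**2. Fixed effects, NCI.** All four row patterns occur among the 80 participants, so the rank is 4 of 4. The group fault does not apply to NCI.

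**3. Reading A: one T9 − T0 difference per participant.** With a participant intercept, the covariance is V = σ²ᵤZZ′ + σ²ₑI. With one row each, Z = I, so ZZ′ = I and V = (σ²ᵤ + σ²ₑ)I. Only the sum is identified: 1 of 2 variance components. On simulated data with condition as the only fixed effect, lme4 stops because the number of grouping levels must be smaller than the number of observations.

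**4. Reading B: repeated scores, no time term.** Let the real-versus-VR difference be 0 at T0 (expected under randomisation), δ₁ at T1 and δ₉ at T9. In balanced data with a random intercept, the condition coefficient is the difference in participant means:

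- T0 and T9 only: (0 + δ₉)/2 = δ₉/2
- T0, T1 and T9: (0 + δ₁ + δ₉)/3

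Neither is the difference in T0-to-T9 change, which is δ₉ − 0 = δ₉. For NCI the group coefficient is affected further. Diagnosis is not randomised, so a baseline difference b that stays constant gives (b + b)/2 = b although the difference in change is b − b = 0.

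**5. Repaired model, ADHD only.** Condition, time, condition × time and a participant intercept:

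| Visits | Fixed-effect rank | Variance components |
|---|---|---|
| T0, T9 | 4 of 4 | 2 of 2 |
| T0, T1, T9 | 6 of 6 | 2 of 2 |

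**6. Size of the available contrast.** For a two-sided 5% test with 80% power on change scores (normal approximation), the detectable difference is (1.960 + 0.842) × √(2/n) in SD of change:

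- n = 20 per arm: 2.802 × 0.316 = 0.89 SD
- n = 16 per arm (an illustrative 20% loss): 2.802 × 0.354 = 0.99 SD

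**The case against.** The strongest defence is that one sentence has compressed three outcomes into one model. The Outcomes section, and the start of the same paragraph for ACOS-Self, already tie the scale to the ADHD group, so the authors may have meant the group terms for NCI only. The redundancy would show as soon as the model is run, and the randomised contrast survives. Most of this stands, and it lowers the severity. It does not remove the contradiction: the sentence names all three scales and no other text corrects it.

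A second defence concerns the change score. For the primary outcomes the protocol also speaks of changes between visits while modelling time explicitly, and where it means difference scores, for EEG, it says so. Missing data are to be handled within the mixed model, which suits repeated rows. NCI may also have more than two visits, since the Abstract, Study Design and Discussion suggest repeated or weekly ratings. This stands against claiming that the model cannot be fitted on every reading. It does not rescue the sentence, because repeated scores need time and its interactions.

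A reader might infer that these outcomes have no workable analysis, or that lme4 would refuse all three models. The documents do not support either. The condition effect within ADHD is estimable in a reduced model. The software stop under reading A requires both a single difference score and a random intercept that this sentence does not state. lme4 is named for the primary models only.

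It is also fair to say that the protocol claims no power for these scales, so the detectable differences above are context, not an error in the plan.

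**Conclusion.** The point holds, at moderate severity. Its first part is certain from the text: group and group × condition cannot be estimated for ACOS-Self and AAQoL (rank 2 of 4), and at most a 20-versus-20 comparison of real and VR nature within ADHD is available. It does not extend to the group terms for NCI.

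The second part, covering all three scales, depends on the reading. With difference scores, it rests on the participant intercept of the primary models carrying over; that variance is then not identifiable. With repeated scores, the model can be fitted once the group terms are dropped for the ADHD-only scales, but its condition and group coefficients do not measure change. The sentence needs correcting either way.

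A verdict that the trial or its clinical outcomes are unanalysable would go too far. The data collection is adequate, the Power section treats secondary outcomes as exploratory, and the randomisation, primary analyses and sample size are untouched.

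**What to change.** Split the sentence in two.

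- **ACOS-Self and AAQoL:** analyse ADHD participants only and drop group and group × condition. Fit an LMM to the T0, T1 and T9 scores with condition, time (categorical), condition × time and a participant random intercept. The estimate is the condition difference in T9 − T0 change. A linear model of T9 on condition and T0 is a simple alternative, but it omits participants without a T9 score, whereas the LMM keeps the planned missing-at-random handling. State that the comparison is at most 20 versus 20.
- **NCI:** keep group and condition, and add time and its interactions to the LMM; or use an ordinary linear model of the change score on group, condition and their interaction. Adjusting for baseline NCI across diagnostic groups is best avoided as the default: the groups are not randomised, so it answers a different question from change. State which visits enter the model, since the document describes the NCI schedule in more than one way.

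The cost is a few sentences of analysis wording, with no change to recruitment, visits or sample size. It should be made before outcome data are available.

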## Results

The project received funding in May 2025. Participant recruitment is anticipated to begin in January 2026, followed by data collection starting in April 2026 to ensure suitable outdoor environmental conditions. Given the minimal-risk, single-session nature of the intervention, no independent data monitoring committee has been established; safety is overseen by the principal investigator, and all adverse events are recorded and reviewed after each session. Data analysis will proceed thereafter, and the study results are expected to be published in May 2028.

## Discussion

This study addresses a key gap in understanding how nature, both physical and virtual, interacts with distinct neurocognitive profiles to influence cognition, well-being, and brain activity. By combining behavioral tasks, self-report and symptom measures, and mobile EEG, it is designed to test whether VR-simulated nature can reproduce the short-term cognitive and neural changes associated with real-world natural exposure and whether it does so via similar or different processes. Rather than treating VR as a straightforward substitute, the protocol explicitly compares patterns of attentional engagement, alpha-based indices of restoration, and symptom-related variability across the 2 exposure types.

Focusing on adults with ADHD is intended to add both scientific and clinical value. Scientifically, it allows examination of how environmental stimulation interacts with atypical attentional and regulatory systems, using both diagnostic group comparisons and dimensional modeling of ADHD symptom scores. Clinically, it explores whether a single, low-intensity nature-based session, real or virtual, may support attentional regulation and quality of life in a population often underserved by traditional therapeutic approaches. Including both ADHD and neurotypical participants and analyzing symptom dimensions across the full sample should help distinguish effects that are broadly shared from those that are amplified or attenuated in ADHD.

The protocol also extends current work on nature exposure by combining immediate postexposure assessments with an 8-week follow-up. Weekly online measures of mood, stress, cognitive complaints, and nature connectedness (including self-reported contact with real and VR nature) will allow us to explore how any initial benefits change over time and whether decay patterns differ by exposure condition or symptom profile. These longitudinal data are exploratory rather than confirmatory but may provide useful information for designing the frequency and “dose” of future nature-based interventions.

In parallel, the integration of mobile EEG in both real and VR settings is intended to provide converging neurophysiological evidence on attentional engagement restoration. Alpha power and related spectral measures will be examined alongside behavioral and self-report outcomes, with the aim of identifying neural signatures that correspond to subjective restoration or cognitive effort. Although the EMOTIV FLEX system offers only moderate spatial resolution compared with laboratory-based EEG, its portability enables ecologically valid recording during naturalistic exposure, which is central to the aims of this protocol.

Several limitations should be acknowledged. The study compares real nature with VR-simulated nature but does not include a nonnature digital control condition, which limits inferences about whether observed effects are specific to natural content vs immersion or digital engagement more broadly. Individual differences in sensory sensitivity and simulator sickness may affect responses to the VR condition despite screening, safety monitoring, and the use of a relatively short (20-minute) exposure. EEG collected during movement-constrained outdoor and VR sessions will still be susceptible to muscle and motion artifacts, and results will depend on rigorous preprocessing and conservative quality control. Conducting the real-nature condition outdoors inevitably introduces variability in weather, temperature, light, ambient noise, and unexpected stimuli. To limit extreme discrepancies, data collection will be scheduled within months of relatively stable weather, sessions will be arranged flexibly to avoid adverse conditions, and key environmental characteristics (eg, temperature, wind, noise level, and light intensity) will be logged to support transparent reporting and exploratory adjustment. In addition, although dimensional modeling improves ecological and theoretical validity, estimates of interaction effects may be constrained by the planned sample size and by measurement noise in self-report data.

Despite these constraints, the study is expected to make a cautious but meaningful contribution to environmental neuroscience, digital health, and neurodiversity research. By directly comparing real and VR nature in adults with and without ADHD, and by tracking both short-term changes and their subsequent attenuation, the protocol aims to clarify when VR can approximate the benefits of real nature and when modality or cognitive profile matters. The findings may help to refine hypotheses about the mechanisms of nature-related restoration and to inform pragmatic decisions about when immersive VR is a suitable, acceptable, and safe option for expanding access to nature-based experiences.

## Appendix

Multimedia Appendix 1 SPIRIT (v2025) checklist.

## Abbreviations

AAQoL: Adult ADHD Quality of Life Questionnaire
ACOS-Self: ADHD Clinical Outcome Self-Report
ADHD: attention-deficit/hyperactivity disorder
ANZCTR: Australian New Zealand Clinical Trials Registry
ART: Attention Restoration Theory
ASRS: Adult ADHD Self-Report Scale
DSM-5: Diagnostic and Statistical Manual of Mental Disorders, Fifth Edition
EEG: electroencephalography
EMA: ecological momentary assessments
ERP: event-related potential
fMRI: functional magnetic resonance imaging
GDPR: General Data Protection Regulation
GHQ-12: General Health Questionnaire-12
LMM: linear mixed-effects model
NCI: Nature Connection Index
SRT: Stress Reduction Theory
VR: virtual reality
VRSQ: Virtual Reality Sickness Questionnaire
